### *Diagnostic value of bedside-US and ULDCT in diagnosing pneumonia*

The radiological findings will be described systematically using standardized assessment templates for US, ULDCT and HRCT. The project assistant will describe the bedside US findings, and radiologists will describe the ULDCT and HRCT diagnosis with standardized relevant clinical information. The US operators and the MRI-operator will be blinded to the results of each other. Study consultants with experience in lung imaging will post-process describe the scans and video clips systematically using developed research templates.

A reference diagnose for pneumonia is defined by a panel of experts. The experts are two consultants from Emergency Departments, who individually will determine if the diagnose was pneumonia, or not. The final diagnoses will be based on all available relevant information including e.g. results of imaging, blood sample and clinical information. A standardized template will be used. Disagreement will be discussed until a consensus is reached.

The results from bedside US and ULDCT of thorax are compared with HRCT of thorax and the reference diagnose. The advantages and disadvantages of the diagnostic capability of the individual modalities are described.

It is assumed that the reference diagnosis finds 98% of patients and index test 90%. With a power of 80%, at least 132 patients should be included (one-sided McNemar test).

The primary outcome is sensitivity and specificity, LLR+, LLR-, AUC for diagnosing pneumonia. To test the hypothesis a chi-squared test will be performed.

Secondary outcome will be sensitivity and specificity for chest x-ray. All outcomes will be reported with corresponding confidence intervals when relevant. Secondary analysis will compare sensitivity, specificity, ROC curve and AUC for ULDCT or bedside US compared to chest x-ray, using McNemar Chi-square to test the null-hypothesis

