### ***Additional imaging if suspected pneumonia***

Bedside US of the lung will be a FLUS (Focused Lung UltraSound), which examines exclusively for life-threatening conditions. FLUS is used to diagnose pneumothorax, pleural effusion and interstitial syndrome. Video clips will be stored during the scan.

ULDCT of thorax will be performed by a radiologist. The patient will be in horizontal rest. The first 10 participants on each site will enter a pilot study to ensure the best possible image quality of ULDCT via customization of the CT, which are different at each hospital. This to ensure uniform quality and dose. A specially designed technical ULDCT protocol has been developed using a breast phantom (N1 'Lungman', Kyoto Kagaku, Japan) equivalent to an 80 kg man. To develop the protocol a GE Revolution CT (GE Healthcare, Waukesha, IL, USA) with 350 mm scan area and 128x0.625mm detector has been used. The ULDCT will be performed with a fixed tube and without a planning image.

As reference standard a High Resolution Computed Thermography HRCT scan of thorax will be taken at the same time as ULDCT on the same scanner. HRCT will be performed according to standard clinical protocols at each hospital, but only doing inspiration to limit radiation.

The three scans will take place within 24 hours after study recruitment. The results of bedside US, ULDCT, and HRCT will be available to the treating physician, when described. If a result requires immediate action, the clinician will be contacted directly by the examiner. If the participant is discharges from the hospital before the scans have been performed, the scan are offered on an outpatient basis.

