### ***Additional imaging if suspected pyelonephritis***

Bedside US of the kidneys will be performed in order to assess whether hydronephrose is present or not. Video clips will be stored during the scan.

An advanced US will be performed at the Radiology Department, and includes Doppler with spectral assessment and registration of RI and PI values in upper, middle, and lower parts of kidneys. It also includes a CEUS (contrast enhanced US) with intravenous injection of 1.5 mL ultrasound contrast. The advanced US will be performed in order to identify inflammatory changes in the kidneys. Video clips from the advanced US will be stored in the Picture Archiving and Communication System (PACS). Clips from CEUS will furthermore be exported anonymously to an external software application (Vuebox) for post-process evaluation.

As reference standard a MRI of the kidneys will be performed at the Radiology Department at the same time (as close as possible) as the advanced US. The scan will include following sequences: planning, Dixon, T1 mapping, T2, T2 mapping, diffusion ADC (100, 400, 800), MRA (3D VIBE angio), and Phase Contrast.

The three scans will take place within 24 hours after study recruitment. The physician responsible for the treatment of the patient, will be informed of the results of the US scans and if MRI, when described. If a result requires immediate action, the clinician will be contacted directly by the examiner. If the participant is discharged from the hospital before the scans have been performed, the scan are offered on an outpatient basis.

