#### *Diagnostic value of bedside US and advanced US in diagnosing pyelonephritis*

The radiological findings will be described systematically using standardized assessment templates for bedside US, advanced US, and MRI. The project assistant will describe the bedside US findings, and radiologists will describe the advanced US and MRI findings with standardized relevant clinical information. The US operators and the MRI-operator will be blinded to the results of each other. Study consultants with experience in kidney imaging will post-process describe the scans and video clips systematically using developed research templates.

A reference diagnose for pyelonephritis is defined by a panel of experts. The experts are two consultants from Emergency Departments, who will determine the final diagnoses based on all available relevant information including e.g. results of imaging, blood sample and clinical information. A standardized template will be used. Conflicts will be discussed until consensus is reached.

The results from bedside US and advanced US of kidney are compared with results from the MRI and reference diagnose. The advantages and disadvantages of the diagnostic capability of the individual modalities are described.

It is assumed that the reference diagnose finds 98% of patients and index test 90%. With a power of 80%, at least 132 patients must be included (one-sided McNemar test).

Primary outcome is sensitivity and specificity, LLR+, LLR-, ROC curve and AUC for diagnosing pyelonephritis. To test the hypothesis a chi-squared test will be performed.

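### The imaging primary outcome has two unranked references, a scan (HRCT or MRI) and an expert panel, and does not say which one defines sensitivity and specificity

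*Protocol*

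**What the plan says.** In the protocol's procedure sections, the reference is a scan. Under Additional imaging if suspected pneumonia: "As reference standard a High Resolution Computed Thermography HRCT scan of thorax will be taken at the same time as ULDCT". Under Additional imaging if suspected pyelonephritis: "As reference standard a MRI of the kidneys will be performed at the Radiology Department".

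In the outcome sections, a second reference appears. For the lung track: "A reference diagnose for pneumonia is defined by a panel of experts". For the kidney track: "A reference diagnose for pyelonephritis is defined by a panel of experts". In both tracks the panel is two Emergency Department consultants who settle disagreements by consensus. On what they may see, the lung section says: "The final diagnoses will be based on all available relevant information including e.g. results of imaging, blood sample and clinical information". The kidney section is worded to the same effect.

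Both outcome sections then plan both comparisons. For the lung: "The results from bedside US and ULDCT of thorax are compared with HRCT of thorax and the reference diagnose". For the kidney: "The results from bedside US and advanced US of kidney are compared with results from the MRI and reference diagnose".

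The primary outcome is stated once per track, as sensitivity, specificity, likelihood ratios and AUC for diagnosing pneumonia or pyelonephritis. It names no reference. The sample-size sentence assumes that the reference diagnosis finds 98% of patients and the index test 90%, and arrives at 132 patients with 80% power and a one-sided McNemar test.

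**The concern.** Sensitivity and specificity have no meaning until the reference is fixed, because the reference decides who counts as diseased. The two references also answer different questions: whether ULDCT or advanced US reproduces the better scan, and whether it identifies patients who have the disease.

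Followed as written, the plan produces two sets of accuracy figures for each index test, both with a claim to be the primary result. Nothing prevents the more favourable set from being chosen after the data are seen.

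**Working it through.** **1. The plan's own figure.** Inputs from the outcome sections: 98% v 90%, power 80%, one-sided McNemar. No alpha is given there, so 0.05 is assumed, the value used for the infection markers. With the two results independent, the discordant cells are 0.98 × 0.10 = 0.098 and 0.02 × 0.90 = 0.018. Their sum is 0.116 and their difference 0.08.

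- N = (1.645√0.116 + 0.842√(0.116 − 0.08²))² / 0.08² = 110.
- With continuity correction, N = 134, close to the stated 132.
- A continuity-corrected comparison of two unpaired proportions gives exactly 132, but per group.

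The number of patients is not in dispute here.

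**2. Does the sample-size sentence choose the reference?** It mentions only the reference diagnosis, which points to the panel. But a panel that defined disease would find 100% of cases by construction. A rate of 98% treats the panel as a fallible test against some further truth, so the sentence does not tie the primary sensitivity and specificity to the panel.

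**3. Same reads, two references, no incorporation.** Assume the index test has Se = Sp = 0.90 against HRCT. This is an assumption; the plan's 90% is a detection rate, not accuracy against HRCT. Let HRCT agree with the panel in a proportion h of panel-positive and of panel-negative patients, and let index test and panel be independent given HRCT. Then

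Se against panel = h × 0.90 + (1 − h) × 0.10, and Sp is the same by symmetry. LR+ = Se / (1 − Sp).

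| h | Se and Sp against panel | LR+ (9.0 against HRCT) |
|---|---|---|
| 0.98 | 0.884 | 7.6 |
| 0.95 | 0.86 | 6.1 |
| 0.90 | 0.82 | 4.6 |
| 0.80 | 0.74 | 2.8 |

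**4. Same reads, panel influenced by the index test.** The panel may use imaging results, and the index tests are not excepted. Assume HRCT prevalence of 50%, and let the panel side with the index test in a share x of the index–HRCT disagreements. Then Se = Sp = 0.90 + 0.10x.

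- x = 0.10: 0.91
- x = 0.25: 0.925
- x = 0.50: 0.95 (LR+ = 0.95/0.05 = 19)

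Steps 3 and 4 together give 0.74 to 0.95, on either side of 0.90. The same arithmetic applies to MRI in the kidney track.

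**5. Who can be scored.** Population and eligibility criteria excludes under-40s, previously included patients and pregnant women from ULDCT and HRCT, but not from bedside lung US. For bedside lung US, such patients can be scored against the panel but not against HRCT. Ethical considerations and risks instead excludes under-40s from track A altogether, so the two sections conflict. For ULDCT these exclusions create no split, because they remove index test and HRCT together.

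**6. Kidney bedside US.** Additional imaging if suspected pyelonephritis, and objective 6, give its purpose as detecting hydronephrosis. The outcome section nevertheless compares it with MRI and the panel under a primary outcome about pyelonephritis.

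**The case against.** Both comparisons are openly planned side by side, and reporting both is legitimate. The text also leans to the panel: the outcome is worded as diagnosing the disease, and the sample-size sentence names only the reference diagnosis. A ranking could sit in a statistical analysis plan that is not shown. The first two points stand and narrow the issue to ranking. The third carries less weight, because the protocol does more than omit a detail: it applies the label of reference to two different things and lets both feed one primary outcome.

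Several stronger readings are tempting but not supported:

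- A reader might infer that the outcome sections replace HRCT and MRI with the panel. They list both.
- A reader might infer that every index test is evaluated in two different populations. The stated exclusions separate them only for bedside lung US. In the kidney track, MRI contraindications and pregnancy are listed as exclusions for suspected pyelonephritis without being limited to one scan. Recruitment allows consent to individual parts, which could separate populations for any test, but the document gives no basis for sizing this.
- A reader might take 98% as the rate at which HRCT finds panel-diagnosed pneumonia. The figure belongs to the reference diagnosis, which is the panel; no HRCT–panel rate is given.
- A reader might expect accuracy against the panel to be lower. Step 4 shows that it could be higher.

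**Conclusion.** The point holds for both tracks: two references, both used, neither named for the primary outcome. Each index test has two candidate primary results, and the headline can be chosen after the data are seen.

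The size and direction of the difference are unknown, because they depend on agreement between HRCT or MRI and the panel. Under the assumed scenarios the shift runs from about 2 points down (98% agreement) to 16 points down (80% agreement), and up to 5 points up if the panel sides with the index test in half of the disagreements. That one result would be very different from the other is a possibility, not something the document shows. The sample size is unaffected.

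**What to change.** In the two imaging outcome sections, name one reference as primary for each index test and make the other comparison secondary. The panel diagnosis fits the stated outcome and is the reference that the sample-size sentence mentions. If it is chosen:

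- In the two additional-imaging sections, relabel HRCT and MRI as comparator scans. Report agreement of ULDCT with HRCT, and of advanced US with MRI, as secondary, in patients who had both scans.
- State that the panel's primary diagnosis is made without the index-test results (bedside US, ULDCT, advanced US), to avoid incorporation bias.
- Give kidney bedside US its own target and reference, since its stated purpose is hydronephrosis.
- For bedside lung US, state which patients enter each comparison. Reconcile the under-40 exclusion between Population and eligibility criteria and Ethical considerations and risks.

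The cost is wording, with no new patients or measurements. Masking the panel does need some preparation of the case material, because the scan results are made available to the treating physician and so may appear in the notes. The downside is that one planned comparison loses primary status, and the headline accuracy may come out higher or lower than under the other reference.

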### *Diagnostic value of infection markers*

The concentration of PCT, CRP, and suPAR are evaluated for the verified diagnosis of pneumonia/pyelonephritis and compared to a control group using receiver-operating characteristic (ROC) curves and identifying an optimal cut-off. Secondary outcomes will evaluate which infection marker in combination of severity scores can assess disease severity and predict short-term and long-term mortality in pneumonia patients.

The study is designed to be able to find a difference in Area under the curve (AUC) from 0.7 to 0.8 between two tests, which requires 200 verified pneumonia cases and 200 controls (power 0.8, alpha 0.05, AUC below 0 hypothesis 0.7) and 150 verified pyelonephritis cases and 150 controls (power 0.8, alpha 0.05, AUC below 0-hypothesis 0.6) (45).

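### Both imaging objectives are sized on a 98% v 90% contrast of the index test against the panel diagnosis that defines disease, which does not size sensitivity, specificity or AUC

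*Protocol*

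**What the plan says.** The Protocol, under Diagnostic value of bedside-US and ULDCT in diagnosing pneumonia, makes the reference diagnosis a consensus of two emergency consultants who use all available information, imaging included. The size is then set in two sentences: "It is assumed that the reference diagnosis finds 98% of patients and index test 90" per cent, and "With a power of 80%, at least 132 patients should be included (one-sided McNemar test").

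The outcome sentence reads: "The primary outcome is sensitivity and specificity, LLR+, LLR-, AUC for diagnosing pneumonia". The test sentence is: "To test the hypothesis a chi-squared test will be performed". A secondary analysis compares sensitivity, specificity, ROC curve and AUC of ULDCT or bedside US with those of chest X-ray, "using McNemar Chi-square to test the null-hypothesis".

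The section Diagnostic value of bedside US and advanced US in diagnosing pyelonephritis repeats the sizing ("It is assumed that the reference diagnose finds 98% of patients and index test 90" per cent; "With a power of 80%, at least 132 patients must be included (one-sided McNemar test")), with the same kind of primary outcome and the same unspecified chi-squared test. It has no secondary McNemar sentence.

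Neither section gives an alpha or a discordant proportion. The sections on additional imaging also call HRCT and MRI the reference standard.

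**The concern.** A sample size should follow from the quantity to be estimated or the hypothesis to be tested. Here the primary outcome is the accuracy of an index test judged against a reference, but the sizing treats the reference as a competitor that itself misses 2% of patients. No truth is named against which the panel could miss them.

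The consequence depends on whom the 132 are:
- If they are reference-positive patients, the reference column is positive throughout, and the McNemar test only shows that the index test missed some cases.
- If they are all suspected patients, McNemar compares the two positivity rates, and false positives of the index test cancel its misses.

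Neither reading sizes sensitivity, specificity, likelihood ratios or AUC. The same paragraph underlies the pneumonia and pyelonephritis imaging objectives (objectives 4 and 5), so neither has a sample-size justification tied to its own outcome. The tests have a related problem: McNemar is named for the sizing, a chi-squared test of an unstated hypothesis for the primary analysis, and McNemar again for ROC curves and AUC, although it compares only paired binary results.

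**Working it through.** **Inputs.** From both imaging sections: proportions 0.98 and 0.90, difference d = 0.08, power 80%, one-sided, N = 132. Alpha is not given there. I assume one-sided 0.05, the level in the biomarker section ("power 0.8, alpha 0.05, AUC below 0 hypothesis 0.7"), and show one-sided 0.025 as the range. Discordance pd is not given. The margins allow 0.08 (every reference miss is also an index miss) to 0.12 (no shared misses); independent errors give 0.98 x 0.10 + 0.02 x 0.90 = 0.116.

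**1. Reproducing 132.**

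Two independent proportions, one-sided 0.05, mean proportion 0.94:
- n = [1.645 x sqrt(2 x 0.94 x 0.06) + 0.842 x sqrt(0.98 x 0.02 + 0.90 x 0.10)]^2 / 0.08^2 = 107.9.
- Continuity correction n/4 x [1 + sqrt(1 + 4/(n x d))]^2 gives 131.7, so 132 per group.

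McNemar, n = [za x sqrt(pd) + zb x sqrt(pd - d^2)]^2 / d^2:

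| One-sided alpha | pd 0.08 | pd 0.110 | pd 0.116 | pd 0.12 |
|---|---|---|---|---|
| 0.05 | 76 | 105 | 110 | 114 |
| 0.025 | 96 | about 132 | 140 | 145 |

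At one-sided 0.05 the uncorrected formula would need pd = 0.139 to reach 132, above the feasible maximum of 0.12. With the same continuity correction it gives 134 at pd = 0.116 and 132 at pd = 0.114. So 132 equals the unpaired corrected size per group, but McNemar routes also reach it.

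**2. Power of 132 pairs for the literal 98% v 90% contrast** (exact one-sided McNemar):

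| One-sided alpha | pd 0.08 | pd 0.116 | pd 0.12 |
|---|---|---|---|
| 0.05 | 98% | 84% | 82.5% |
| 0.025 | 96% | 74% | 72.5% |

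**3. What the test does when the reference defines disease.** Among 132 reference-positive patients every discordant pair is an index miss, so with m misses the exact one-sided p is 0.5^m. Four misses give 0.0625 and five give 0.031, so the test is significant from five misses on.
- True sensitivity 90%: P(Binomial(132, 0.10) >= 5) = 99.8%.
- True sensitivity 95%: P(Binomial(132, 0.05) >= 5) = 79%.

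A good index test is therefore usually declared different from the reference, and the result does not say how accurate it is.

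**4. Precision the study could state instead** (95% Wilson interval around a sensitivity of about 90%):
- 132 reference-positive patients (119/132): 84-94%.
- If the 132 are suspected patients, the number of cases depends on prevalence, which is an assumption. At 40%, 53 cases (48/53) give 80-96%; at 60%, 79 cases (71/79) give 81-95%; at 80%, 106 cases (95/106) give 82-94%.

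**5. Cases that may be imaged.** The introduction to Outcomes and statistical analysis expects at least 250 pneumonia and 150 pyelonephritis diagnoses. Reaching 132 imaged pyelonephritis cases would need 132/150 = 88% to complete imaging.

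**The case against.** The strongest defence is that the primary outcome is estimation. The pneumonia section already promises confidence intervals and sets no success criterion, so a poorly described test does not stop the accuracy estimates from being produced. That stands, and it limits the harm: a reader might infer that the trial could succeed by showing its new test to be worse, but the text contains no such rule.

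A second defence is that the 98% was loosely meant for HRCT or MRI, judged against the panel. That would make a coherent paired comparison of sensitivities. However, the sentence names the reference diagnosis, which the same section has just defined as the panel consensus, and even on this reading specificity and AUC are not sized.

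Three stronger readings are tempting and not supported:
- That 132 cannot be a McNemar number. Corrected McNemar at one-sided 5% gives 132 at a feasible discordance of 0.114, and uncorrected McNemar at one-sided 2.5% gives it at about 0.110. The match with the unpaired formula does not prove origin.
- That the primary test is an unpaired chi-squared test. The text says only chi-squared, and McNemar is itself one. Naming McNemar only for the secondary comparison makes the primary test ambiguous, not demonstrably unpaired.
- That there is no valid size at all. At one-sided 5%, 132 pairs give at least 82% power for the literal contrast at every feasible discordance.

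An unseen analysis plan may specify the primary test. It would not repair the contrast or the use of McNemar for AUC, both of which the protocol states.

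**Conclusion.** The point holds in this form: the defect is the contrast more than the number. Setting the index test against the diagnosis that defines disease does not size the stated primary outcome in either imaging section. If the 132 are reference-positive, the test is significant 99.8% of the time at 90% sensitivity and 79% at 95%, assuming one-sided 5% and an exact test.

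Three further points stand. The figure 132 cannot be verified as a McNemar size, because alpha and discordance are missing. The counted population is not stated as suspected patients or verified cases. The primary chi-squared test is ambiguous and has no hypothesis. In the pneumonia section only, McNemar is named for ROC curves and AUC, which it cannot test; that is a secondary analysis.

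The arithmetic does not support a claim that the study is too small for the literal contrast at one-sided 5%. At one-sided 2.5%, power would range from 72.5% to 96%.

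**What to change.** In both imaging sections, replace the 98% v 90% power sentence with a precision statement for the expected number of imaged reference-positive patients. For example: 132 such patients give a 95% CI of about 84-94% around a sensitivity of 90%, and 79 give 81-95%. Do not present 132 as guaranteed.

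Delete the chi-squared test of index against reference, and report sensitivity and specificity with confidence intervals.

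In the pneumonia section, compare ULDCT or bedside US with chest X-ray by McNemar separately in reference-positive patients (sensitivity) and reference-negative patients (specificity). Compare AUCs with a paired test such as DeLong.

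The cost is protocol wording and the loss of the 80% power claim. A reader might infer that no further patients could be needed, since 250 and 150 cases are expected. The documents do not establish this: those are diagnoses in the whole study. Under Population and eligibility criteria, patients under 40 and pregnant women get no CT, and track B has MRI, contrast-allergy and pregnancy exclusions. Recruitment allows consent to individual parts, and some scans are offered only after discharge. The achieved precision will depend on how many cases complete imaging.
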